**Fig. 1 Fig1:**
[figure not shown]
Consolidated Standards of Reporting Trials (CONSORT) diagram

### Intervention group

#### Multi-component exercise programme

The 52-week exercise programme will consist of two gym-based sessions and one home-based session per week. During the first 26 weeks, the two gym-based sessions will be supervised by an accredited exercise physiologist (tertiary-trained exercise professional) in a community-based health and fitness facility. For the final 26 weeks, only one gym-based session will be supervised. All home-based sessions will be unsupervised and performed in the participant’s own time. All intervention-group participants will be provided with a yearly membership at a community-based health and fitness centre and will have the opportunity to complete their home-based sessions in this setting at their own discretion.

The exercise training programme is a multi-component programme that will follow key training principles of specificity and progressive overload and will be individually tailored to the participant’s health and functional status. The programme will follow similar exercise prescription guidelines in terms of the structure, type and dose (frequency, sets, repetitions, intensity) of training to our previous ‘*Osteo-cise*: Strong Bones for Life’ community-based osteoporosis prevention exercise programme in healthy older adults in which we observed significant improvements in musculoskeletal health and function (Table 1) [39, 54, 55]. To ensure progressive overload and promote a sense of achievement for the men, the 52-week programme will be divided into five mesocycles (training phases). The first mesocycle (4 weeks – adoption phase) will focus on orientation to the exercise programme, with an emphasis on correct technique. The four subsequent 12-weekly mesocycles will focus on progression through three 4-weekly microcycles (preparatory phase, challenge phase and consolidation phase). Each gym-based session (approximately 60 min) will consist of a warm-up and cool-down and a combination of aerobic training, PRT, weight-bearing, impact activities and challenging balance/functional exercises. More specific details about each training component are provided below.

**Table 1 Tab1:** Structure of the exercise programme and training doses for 52 weeks

Phase			Aerobic training		Progressive resistance training					Weight-bearing, impact training			Functional and core stabilisation training	
Microcycle	Week	Mesocycle	Duration	%HR_MAX_	Sets	Reps	RPE^1^	Speed^2^	Rest	Sets	Reps	Intensity^3^	Sets	Duration/reps
#1	1–4	Orientation	15–25 min	55–75%	2	12–15	3–4	Slow	1–2 min	3	10–20	Low	2	Balance exercises, 30–60 s or until fatigue Core stabilisation exercises, 10–15 reps or up to 50 for abdominal based exercises
#2	5–8	Preparatory	15–25 min	60–75%	2	10–-15	3–4	Slow	1–2 min	3	10–-20	Low to moderate	2	
	9–12	Challenge	15–25 min	60–75%	2	8–12	5–8	Rapid	2 min	3	10–20		2	
	13–16	Consolidation	15–25 min	60–75%	2	8–12	5-8	Rapid	2 min	3	10–20		2	
#3	17–20	Preparatory	15–25 min	60–75%	2	10–15	3–4	Slow	1–2 min	3	10–20	Moderate	2	
	21–24	Challenge	15–25 min	60–75%	2	8–12	5–8	Rapid	2 min	3	10–20		2	
	25–28	Consolidation	15–25 min	60–75%	2	8–12	5–8	Rapid	2 min	3	10–20		2	
#4	29–32	Preparatory	15–25 min	60–75%	2	10–15	3–4	Slow	1–2 min	3	10–20	Moderate to high	2	
	33–36	Challenge	15–25 min	60–75%	2	8–12	5–8	Rapid	2 min	3	10–20		2	
	37–40	Consolidation	15–25 min	60–75%	2	8–12	5–8	Rapid	2 min	3	10–20		2	
#5	41–44	Preparatory	15–25 min	60–75%	2	10–15	3–4	Slow	1–2 min	3	10–20	High	2	
	45–48	Challenge	15–25 min	60–75%	2	8–12	5–8	Rapid	2 min	3	10–20		2	
	49–52	Consolidation	15–25 min	60–75%	2	8–12	5–8	Rapid	2 min	3	10–20		2	

Adapted from Gianoudis et al. ^1^RPE: Rating of Perceived Exertion (1–10); ^2^Speed: slow (2–3 sec concentric and 2–3-s eccentric contractions), rapid (rapid concentric and 2–3-s eccentric contractions); ^3^Intensity: low (ground reaction force (GRF) ~ 1–3 × body weight), moderate (GRF ~ 3–6 × body weight), high (GRF ~ 6–9 × body weight)

#### Aerobic training

For the aerobic exercise, participants will be prescribed 15 to 25 min of continuous aerobic training at 55–75% of predicted heart rate maximum via modalities such as stationary cycling, treadmill walking or rowing. The type of aerobic exercise prescribed will be based on each participant’s preference and functional capabilities.

#### Progressive resistance training

For PRT, participants will be prescribed five or six targeted hip, spine and forearm resistance exercises using machine and free weights (two sets of 12–15 repetitions at moderate intensity (3-4 on the 10-point Rating of Perceived Exertion (RPE) scale) for each exercise for the first 4-8 weeks, progressing to two sets of 8–12 repetitions at moderate to hard intensity (4–6 on the RPE scale) thereafter; resistance will be increased as tolerated to maintain intensity and ensure progressive overload). During the first mesocycle, five resistance exercises will be available to choose from for each training session (leg press, bench press, one hip-targeted, one-spine targeted and one upper body exercise). New resistance exercises will be introduced at the start of each subsequent mesocycle (three hip-targeted, three spine-targeted and one upper- body-targeted). Varying combinations of the nine resistance exercises in each of these mesocycles will be prescribed each session. After the initial 8 weeks of training, participants will be progressively taught to perform the concentric (lifting) phase of all lower body exercises at high velocity. This is designed to improve movement speed and muscle power. When possible, participants will perform resistance exercises standing with the aim to also improve balance and physical function.

#### Weight-bearing, impact exercise

For the weight-bearing, impact-loading exercises, participants will be prescribed three exercises (interspersed amongst the PRT exercises) consisting of three sets of 10–20 repetitions that will utilise body weight as the primary load. The programme will focus on lower-limb exercises designed to load the hips. The exercises prescribed will be based on a battery that we have previously shown to be safe and effective for improving femoral neck and lumbar spine aBMD in older men [54]. This battery includes a range of exercises from low to high intensity (magnitude of peak ground reaction forces) and difficulty (easy, moderate, hard) and is divided into three broad categories: stationary movements (e.g. marching on the spot, mini-tuck jumps), forward/backwards movements (e.g. forward bench step-ups, drop jumps) and lateral movements (e.g. side-to-side jumping). Training intensity will be increased progressively by increasing the height of jumps, by adding additional weight, increasing the rate of impact-loading or multi-directional movement patterns (e.g. diagonal loads).

#### Challenging balance/functional exercise

Challenging balance and functional exercises will include a range of static and dynamic exercises, including fit ball exercises (e.g. sitting on fit-ball with knee extension), standing balance activities (e.g. single-leg standing) and dynamic functional tasks (e.g. heel-to-toe walking). Participants will be prescribed two exercises per session and asked to complete two sets of 30–60 s or for a given number of repetitions. To ensure progression, participants will be prescribed a new exercise or advance to a more challenging level (e.g. closing eyes, reducing base of support, confounding visual fixation, changing centre of mass or adding a second manual or cognitive task) once they have mastered the previous exercise (e.g. it is no longer challenging).

#### Core stabilisation exercise

Key muscle groups known to help maintain good posture, improve pelvic floor function and trunk stability (e.g. rotator cuff, scapular stabilisers, transverse abdominis, pelvic floor muscles) will be targeted with these exercises, which are important for balance and muscular performance [56]. Participants will be prescribed two exercises per session with light to moderate resistance in two sets of 10 to 15 repetitions. Of note, abdominal-based exercises will be prescribed in two sets of up to 50 repetitions.

#### Home-based exercise programme

The home-based exercise programme will consist of similar types of exercise to the gym-based sessions, but body weight and resistive tubing (provided to participants) will be used for resistance exercises. This will provide participants with knowledge and experience of ways to exercise relatively inexpensively in a home-based setting following the completion of the study. The home-based programme will be explained and demonstrated to the participants during the initial gym-based sessions and instructions will be provided. Three resistance exercises, three weight-bearing, impact-loading exercises and three functional exercises following the same training principles as gym-based sessions will be prescribed for each home-based session. The home-based programme will be progressed and new exercises will be introduced once the previous exercises are no longer challenging for the participant.

#### Nutritional supplement

The nutritional supplement will consist of a daily whey-protein-, calcium- and vitamin D-enriched drink (powder) combined with a single vitamin D tablet. Participants will be provided with 6-monthly supplies of powder in single-use sachets and tablets. Each sachet is to be mixed with 150 ml of water and shaken vigorously in a ‘shake-and-take’ container (provided to participant). Each sachet of powder will contain approximately 25 g of whey-protein concentrate 80% (WPC80), containing approximately 2.4 g of leucine, 1200 mg calcium carbonate (~ 480 mg elemental calcium) and 1000 IU vitamin D (Omniblend, Campbellfield, VIC. Australia). The vitamin D tablet will contain 1000 IU (Ostelin, Macquarie Park, NSW, Australia). On the non-training days, participants will be asked to take one sachet every morning before breakfast. This is designed to try and ensure a more even protein intake throughout the day which has been reported to optimise muscle protein balance [57]. On exercise training days, participants will be encouraged to consume the sachet within 1–2 h of completing their exercise session as early post-exercise consumption of protein has been shown to promote an increase in MPS and muscle hypertrophy in older adults [58, 59].

### Usual-care control group

Participants allocated to usual care will receive ongoing care from their physician/specialist but will not receive additional education or access to exercise training or the protein-, calcium- and vitamin D-enriched nutritional supplement powder sachet. Due to current practice guidelines [40] and a pilot study we conducted in 31 men undergoing ADT for PCa in which 65% reported taking vitamin D supplementation (90% at least 1000 IU/day), all men randomised to usual care will receive 1000 IU vitamin D per day. There is no evidence that vitamin D alone (without calcium supplementation) at these doses can prevent bone loss in these men [40].

### Measurements

All measures will be collected at baseline, 26 and 52 weeks. Additionally, 24-h food recalls will also be administered at 13 and 39 weeks to monitor any habitual fluctuations in dietary factors. With the exception of blood samples, 24-h food recalls and questionnaires, all data will be collected at Deakin University. Blood samples will be collected at an external commercial pathology clinic. The 24-h food recalls will be administered via telephone. Questionnaires will be completed by participants at home prior to each testing sessions (i.e. baseline, 26 and 52 weeks) and checked by the research staff during these face-to-face testing sessions. A summary of the proposed outcome measures is shown in Table 2. All participants will undergo all measures expect those specific to treatment allocation (i.e. compliance to the intervention). All data collected will be in a continuous format, aside from the outcomes from some of the questionnaires, which will be categorical in nature.

**Table 2 Tab2:** Summary of data collection

Variables	Data collection method	Data collection points		
		Baseline	26 weeks	52 weeks
Primary outcome measures				
Areal bone mineral density	DXA proximal femur and lumbar spine	x	x	x
Secondary outcome measures				
Bone structure and strength	pQCT scan at 4% and 66% radial and tibial site	x	x	x
Body composition	DXA total body and regional lean mass, fat mass and % body fat	x	x	x
	pQCT 66% radial and tibial muscle cross-sectional area and muscle density	x	x	x
Muscle strength	Chest press, leg press and seated row	x	x	x
	Grip strength	x	x	x
Functional capacity	30-s sit-to-stand	x	x	x
	Timed-up-and-go with cognitive task	x	x	x
	Four-square step test	x	x	x
	Berg balance scale	x	x	x
	Four-metre usual walk	x	x	x
	400-metre walk	x	x	x
Biochemistry and lipids	Overnight, fasted serum and plasma collection	x	x	x
Inflammatory markers	Overnight, fasted serum and plasma collection	x	x	x
Blood pressure	Automated measurement	x	x	x
Cognitive function	CogState Brief Battery computerised tests	x	x	x
	Rey Auditory Verbal Learning Test	x	x	x
	Trail Making Test (Part A and B)	x	x	x
	Digit Span Test	x	x	x
	National Adult Reading Test	x		
Health-related quality of life, fatigue and mood	Functional Assessment of Cancer Therapy-Fatigue questionnaire	x	x	x
	Functional Assessment of Cancer Therapy-Prostate questionnaire	x	x	x
	Assessment of Quality of Life 8D questionnaire	x	x	x
	Geriatric Depression Scale questionnaire	x	x	x
	Depression Anxiety and Stress Scale questionnaire	x	x	x
Additional measures				
Anthropometry	Height, weight, Body Mass Index, waist and hip circumference	x	x	x
Habitual physical activity	Community Healthy Activities Model Programme for Seniors physical activity questionnaire	x	x	x
Diet	24-h food recalls	Collected every 13 weeks		
Additional questionnaire	Demographic questionnaire	x		
	Clinical and lifestyle questionnaire	x	x	x
	Sun exposure habits and practices questionnaire	x	x	x
	Alcohol consumption questionnaire	x	x	x
	Medical questionnaire	x	x	x
	Medication questionnaire	x	x	x
	Falls questionnaire	x	x	x
Exercise programme adherence	Calculated from monthly calendars collected every 4 weeks	Collected every 4 weeks		
Supplement compliance	Calculated from supplement returned at 26 and 52 weeks		x	x
Adverse events	Calculated from monthly calendars collected every 4 weeks	Collected every 4 weeks		

*DXA* dual-energy X-ray absorptiometry, *pQCT* peripheral quantitative computed tomography

### Primary and secondary outcome measures

The primary outcome for this study will be changes in proximal femur and lumbar spine aBMD. Secondary outcomes will comprise: changes in 4% and 66% tibial and radial vBMD, bone structure and strength, total body and regional body composition, muscle strength, functional capacity, cardiometabolic health, inflammatory biomarkers, HR-QoL and cognitive function.

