Exercise training has been strongly suggested as a viable intervention to ameliorate many of the adverse effects of ADT [17, 26–28]. In terms of musculoskeletal health outcomes, a number of interventions have shown that progressive resistance training (PRT) can increase muscle strength [29–33], muscle endurance [30, 34] and balance [30] in men treated with ADT. While there is also some evidence that PRT can improve or preserve lean body mass (LBM) [30, 32, 33, 35], a systematic review found that there was inconclusive findings on the effects of exercise training in men treated with ADT on bone health [26]. To date, only four studies have examined the efficacy of exercise training on areal bone mineral density (aBMD) in ADT-treated men, three of which were conducted over interventional periods of no longer than 20 weeks and observed no benefit [32, 36, 37]. This is perhaps not unexpected given that the typical bone remodelling cycle and new steady state that is measurable takes 6–8 months to complete, and thus it is unlikely that any true physiological skeletal adaptations would occur prior to this period. However, a recent 12-month randomised controlled trial (RCT) also reported no marked skeletal benefits of a targeted PRT and impact-loading exercise programme in men treated with ADT [36]. This may be due to a number of factors. First, the sample size of approximately 25 per group was below the target sample which may have limited the power to detect any between-group differences. Second, the impact exercise programme was non-progressive and only consisted of two-footed jumps (plus 10% body weight), and thus did not incorporate diverse loading patterns which are known to be important for bone remodelling. Third, the mean calcium intake was < 750 mg/day, well below the recommended dietary intake of 1200 mg/day. There is some evidence that insufficient calcium intakes can attenuate the skeletal responses to exercise in older adults [38]. Finally, this study was limited to an assessment of aBMD by dual-energy X-ray absorptiometry (DXA), which provides no information on other determinants of bone strength (e.g. trabecular volumetric BMD (vBMD), cortical structure), which may change following exercise training, independent of aBMD. This is important because the findings from a prospective study using high-resolution, peripheral, quantitative computed tomography (pQCT) found that treatment with ADT for 12 months was associated with losses of up to 11.3% in cortical and 3.5% in trabecular vBMD, which are two- to three-fold greater than changes observed in DXA aBMD [14]. In healthy older men, the findings from an 18-month RCT found that a targeted and progressive multi-component exercise programme incorporating PRT and a diverse range of weight-bearing, impact activities was safe and effective for improving lumbar spine trabecular vBMD and femoral neck aBMD, cross-sectional area and strength as well as muscle strength, mass and size [39]. Further long-term RCTs are required to examine whether similar well-designed and progressive multi-component exercise programmes in combination with adequate nutrition can ameliorate bone and muscle loss in men treated with ADT for PCa.

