#### Bone mineral density

Total hip, femoral neck and lumbar spine (L1–L4) aBMD (g/cm^2^) will be assessed using DXA (Lunar Prodigy, GE Lunar Corp., Madison, WI, USA) using software version 12.30.008. The short-term coefficient of variation (CV) for aBMD measures range from 0.6 to 1.0% within our laboratory.

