### Sample size calculation

The sample size calculations are based on our previous research in healthy and ADT-treated men. The mean (standard deviation (SD)) annual loss in femoral neck, hip and spine BMD in ADT-treated men was 3.0% (4.5), 2.6% (2.8) and 3.9% (3.0), respectively [14]. Our previous exercise trials in healthy older men have shown that 12 months of training can increase spine aBMD by 1.5–2.0% (SD 2.9) and hip aBMD by 1.2–1.8% (SD 2.8) [39, 55]. We estimate a conservative net difference in aBMD in favour of the intervention of ~ 3.5–4.0% at the hip and spine. Based on these estimates, 29 men in each group will provide 90% power (*P* < 0.05, two-tailed) to detect a difference of this magnitude (assuming a SD of 4.0). A net benefit of this magnitude is clinically relevant as there is evidence that a 1–2% gain in aBMD translates into a 7–14% reduction in fracture risk [36, 93]. For pQCT bone measures, radial and tibial cortical area decreased by 11.5% (8.8) and 12.5% (7.4), respectively, over 12 months in ADT-treated men [14]. While few long-term trials have examined the effect of exercise training on pQCT bone geometry in older men, several intervention trials in older adults have shown that a targeted, weight-bearing, impact-exercise programme can have beneficial effects on cortical bone [94, 95]. Assuming that the proposed intervention can half the rate of loss in cortical area, we estimate that we will require 39 men per group (SD 8.0; 90% power, two-tailed, *P* < 0.05). Based on a previous study and a meta-analysis showing that ADT is associated with an average 7.7% gain in fat and a 2.8% loss in lean mass over 3–12 months [96, 97], and that exercise training can prevent the gain in FM and increase (1–5%) or preserve LBM relative to usual care in men on ADT [30, 32], we estimate a sample size of 24–32 in each group will be required to observe a preservation in LBM and FM in the intervention group vs. usual care (90% power, two-tailed, *P* < 0.05). Assuming a conservatively projected 30% dropout, an estimated sample size of 51 men per group (102 in total) will be required. Based on previous studies in ADT-treated men focussing on a number of our secondary outcomes [32, 37, 98], we estimate that we will have sufficient power (80–90%, *P* < 0.05, two-tailed) to detect the following intervention effects: 20–40% for muscle strength; 8–22% for functional capacity; 4 points for fatigue (FACT-F), 15% for fasting plasma glucose and 14% for serum IL-6 and 20% for CRP. We will also have sufficient sample to detect a clinically meaningful difference of 0.5 SD in the Assessment of Quality of Life 8D questionnaire (AQoL-8D) and 9 points on the FACT-P (disease-specific QoL).

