
### Statistical analysis

Primary analyses will be conducted on an intention-to-treat basis using STATA statistical software (STATA, College Station, TX, USA). Per-protocol analysis will also be performed by including all participants who are at least 66% compliant to the exercise (two of three sessions per week) and 80% compliant to taking the supplements. Initially, descriptive statistics will be computed to compare the intervention and usual-care groups on background variables and baseline measures. All data will be screened for outliers and the normality of the distribution of all data will be assessed using Kolmogorov-Smirnov tests, with skewed data log transformed prior to analysis. Linear mixed models with random effects will be used to evaluate the effects of the intervention compared to usual control. Potential covariates to be included will be: age, duration of ADT use, other chronic conditions, change in medication and change in habitual physical activity or diet. Where possible, we will obtain endpoint measures from all withdrawals and include all randomised subjects in the final analysis. For participants who are lost to follow-up, missing data will be handled with multiple imputation, with subsequent sensitivity analyses to evaluate the effect of potential non-random attrition. Baseline measures and changes in outcome variables will be presented as means ± SD or 95% confidence intervals. A significance level of *P* < 0.05 will be adopted for all statistical tests.

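### The primary outcome spans two regions measured as three bone sites, each tested at P < 0.05, with no rule on whether one site or all must be significant

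*Protocol article*

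**What the plan says.** Under Primary and secondary outcome measures, the protocol article states: "The primary outcome for this study will be changes in proximal femur and lumbar spine aBMD". The wording is singular, but it covers two regions. The section on bone mineral density lists what the scans will yield: "Total hip, femoral neck and lumbar spine (L1–L4) aBMD". The sample size section gives separate annual losses for the same three sites, then states one target, a "net difference in aBMD in favour of the intervention of ~ 3.5–4.0% at the hip and spine", for which "29 men in each group will provide 90% power" at a two-sided 0.05.

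The statistical analysis section specifies linear mixed models with random effects. It closes with a threshold of P < 0.05 that "will be adopted for all statistical tests".

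Table 2 marks the primary outcome at baseline, 26 weeks and 52 weeks, and no section names one follow-up as primary. The aim, which describes a 12-month trial, and the sample size, built on annual change, both point to 52 weeks.

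**The concern.** A per-test threshold does not say what counts as a positive trial. With two or three primary measures, the article would need to say whether one significant site is enough, whether all are needed, or which is tested first. It says none of these. What it does fix is the full 0.05 for each test.

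Without a success rule, a significant difference at one site out of three could be reported as a positive primary result, and a reader could not tell from the protocol whether that was the intended standard. The error rate of such a claim exceeds 5%. Under the opposite reading, where all sites must be significant, the error is controlled, but the sample size was not calculated for that claim. Either way, the stated pair of 5% error and 90% power does not describe the trial's main conclusion.

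**Working it through.** **Inputs from the article.** Two-sided alpha 0.05 per test (statistical analysis; sample size calculation). Difference 3.5–4.0 percentage points, SD 4.0, 90% power, 29 per group, 51 randomised per group, 30% dropout (sample size calculation). Three sites (bone mineral density; sample size calculation), or two if only the regions count.

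**Assumption.** The correlation r between the test statistics at different sites is not given. The range 0 to 0.9 is shown, with equal correlation between all sites.

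**Step 1: reproduce the stated sample size.** For a two-sample t-test with difference 3.5 and SD 4.0, the noncentrality at n = 29 is 3.5 / (4.0 × √(2/29)) = 3.33. Two-sided power at 0.05 is then 90.6%. At n = 28 it is 89.5%, so 29 is the smallest n that reaches 90%. The stated figure is therefore one comparison at the full 0.05, using the lower end of the effect range.

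**Step 2: error if any one site suffices, at one time point.** With independent sites the chance of at least one false positive is 1 − 0.95^k:
- k = 3: 1 − 0.857 = 14.3%
- k = 2: 1 − 0.9025 = 9.75%

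With correlated sites it is 1 − P(every |Z| < 1.96) under a multivariate normal:

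| r | three sites | two sites |
|---|---|---|
| 0 | 14.3% | 9.75% |
| 0.3 | 13.6% | 9.5% |
| 0.5 | 12.5% | 9.1% |
| 0.7 | 10.9% | 8.3% |
| 0.8 | 9.8% | 7.8% |
| 0.9 | 8.4% | 7.0% |

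**Step 3: power if all sites must be significant.** The chance that every site gives a false positive cannot exceed 5%. Suppose the true difference is 3.5 points with SD 4.0 at each of three sites. Joint power is then at most the single-site power. With independent sites it is the cube of that power:
- 29 per group: 0.906³ = 74%, against 90.6% for one site
- 35 per group: 0.950³ = 86%, against 95.0% for one site

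Positive correlation moves the joint figure up towards the single-site value.

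**Step 4: cost of correcting over three sites.** Completers: 51 × 0.7 = 35.7, so 35 per group. The strictest Holm step is 0.05/3 = 0.0167. At 3.5 points and SD 4.0 the noncentrality is 3.5 / (4.0 × √(2/35)) = 3.66. Power is 88.3% at 0.0167, against 95.0% at 0.05.

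**The case against.** The strongest objection is that the article never says one site is enough. The outcome is worded as a single item covering both regions, which could mean that both must improve, and then the error is not inflated. This stands, and it is why the 8–14% is conditional. It does not remove the problem, because the article does not state the all-sites rule either, and its power figure does not fit that rule.

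A second objection is that the outcome definition names two regions, and that listing total hip and femoral neck as scan results does not make each of them primary. This partly stands. Three is the more natural count because the sample size section also treats three sites separately, but the two-site range of 7–10% belongs beside it.

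A third is that an analysis plan not shown here may settle the matter. Silence could be left to such a plan. A sentence assigning 0.05 to all tests is not silence, and an adjustment elsewhere would conflict with it.

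A reader might also infer that each of the two follow-up visits is a separate route to success, making six tests. The error would then be about 16–20% (site correlation 0.8 to 0.5, visit correlation 0.7, all assumed). The article does not support this. It nowhere offers 26 weeks as a way to win, a mixed model can give one test per site, and the 12-month aim and annual-change sample size imply 52 weeks. Nor does it propose an effect pooled over both visits.

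The Background's remark on skeletal adaptation, that "it is unlikely that any true physiological skeletal adaptations would occur prior to this period", refers to a cycle of 6–8 months. Twenty-six weeks is about 6 months (26/52 × 12), the lower edge of that window, so the remark does not show that the 26-week visit is too early.

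**Conclusion.** The concern holds in conditional form. The article combines a primary outcome of two regions, measured and sized as three sites, with a blanket 0.05 per test and no success rule. If any one site suffices, the false-positive chance at one time point is about 8–14% for three sites or 7–10% for two. No correlation in the assumed range brings it back to 5%. If all sites are required, the error is at most 5%, but the 90% power applies to one comparison and is only an upper limit for the joint claim. An unconditional statement that the trial runs at an inflated error rate would go too far, because the any-site rule is a possible reading and is not in the text. The missing name for the primary time point is a lesser matter of wording, since 52 weeks is already implied.

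**What to change.** State that the primary analysis is the between-group difference in aBMD change at 52 weeks, estimated from the mixed model, with 26 weeks secondary. For the primary outcome, replace the blanket 0.05 with Holm's procedure over total hip, femoral neck and lumbar spine at an overall two-sided 0.05. One named primary site or a fixed testing sequence would serve equally well. Say in the same sentence what will count as a positive primary result.

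The cost is wording and a small loss of power under Holm: about 88% at the strictest step with 35 completers per group, slightly below the stated 90%, against 95% unadjusted. Naming one primary site loses no power at that site. Recruitment was still under way according to the trial status section, so the rule could be set before the data are analysed.
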